## Abstract

**Background:**

The Holocaust was one of the most traumatic catastrophes in recorded human history. Survivors seeking psychotherapeutic help today, now in their seventies and older, often show symptoms of a posttraumatic stress disorder (PTSD), depression, or prolonged grief disorder. Established psychological treatments for PTSD (e.g. cognitive behaviour therapy, psychodynamic therapies) have been tested and assessed mainly with young and middle-aged adults; only very few studies examined them in old age. There is no therapy outcome study known to us for any treatment mode for Holocaust survivors. Moreover, there is a need for an age group-specific treatment of PTSD and other stress-related mental disorders. A narrative approach including life-review and narrative exposure seems to meet very well the natural need of older people to review their lives and is highly effective. However, most studies on the efficacy of life review therapy (LRT) focus on late-life depression. There is a lack of efficacy studies evaluating the effect of LRT on PTSD symptoms in older individuals that have experienced traumatic events.

**Methods:**

The main goal of this study is to evaluate the effect of LRT for Holocaust survivors (LRT-HS) on symptoms of PTSD and related mental health problems (depression, anxiety, prolonged grief), compared to a supportive control group. A secondary goal is to identify the characteristics of participants that seem to especially benefit from the treatment. The proposed study is a randomised, controlled follow-up trial including Holocaust survivors with one or more trauma-related disorders. The LRT treatment consists of 20–25 sessions. Before and after the treatment phase, participants in both conditions will be assessed. Follow-up will take place 6 months after the treatment. A sample size of 80 is required (drop-out rate included).

**Discussion:**

Efficacious treatments for trauma-related disorders in older people are of high importance, also because the probability of traumatisation and loss increases with age. Because this study is conducted with this specific group of multiply traumatised people, we are convinced that the results can easily transfer to other samples.

**Trial registration:**

ISRCTN, ISRCTN12823306. Registered 31 March 2018 – Retrospectively registered (first participant 22 December 2017).

## Background

### The holocaust and its psychological consequences in old age

The Holocaust was one of the most traumatic catastrophes in recorded human history. Over the span of several years, a multitude of traumatic events were experienced by a large group of people: persecution and flight under threat of death, loss of family members, starvation, fighting, rape, forced displacement, concentration or extermination camps, torture, witnessing torture and death and being forced to survive in hiding etc. The majority of Holocaust survivors alive at present (now in their seventies and eighties or older) were children and teenagers during the years of the Holocaust. In addition to experiencing traumatic stressors, being a child or adolescent before, during and even after the Second World War (WWII) also meant experiencing massive losses and being separated from parents, relatives and home [1].

Survivors grown old, seeking psychotherapeutic treatment today, exhibit a deterioration of the capability to deal with the burden of the past by a depressed, or irritable mood as a result of an underlying posttraumatic stress disorder (PTSD). The mental health of Holocaust survivors is in average still worse today than a comparison group, mainly with regard to PTSD symptoms, depression and anxiety [2]. The majority of Holocaust survivors show a chronic course, i.e. they experience a steady decrease of PTSD symptom severity, whereas about 10% of survivors show a delayed course, i.e. symptoms increase over time or get reactivated after a long symptom-free time [3].

Although Holocaust survivors exhibit incredible adaptive processes [4], aging poses new challenges for this adaptation process. Aging is accompanied by reviewing one’s life in order to evaluate gains and losses and find meaning [5]. When old people engage in retrospection, past memories might evoke those early experiences of trauma, loss and deprivation and induce or intensify symptoms of PTSD, anxiety, depression and grief. In addition, confrontation with new crises (e.g. retirement), losses (persons, resources, physical and mental decline) and traumatic events (e.g. wars) might further conjure up those childhood memories and intensify symptoms [6]. Living in Israel is especially characterised by a constant feeling of danger and looming threat due to the political instability and ongoing threat of war in the Middle East.

### State of treatment research

#### Established PTSD treatments

Most PTSD treatment research has focused on children and young and middle-aged adults. The need for psychotherapy for the elderly, especially for those who suffer from PTSD, has not been subject to systematic study up until very recently [7]. Established psychological treatments for PTSD can be roughly divided into (a) trauma-focused approaches including exposure and cognition-focused approaches (e.g. cognitive behaviour therapies, CBT, eye movement desensitisation and reprocessing and narrative exposure) and (b) approaches with a broader focus, i.e. not only on the trauma, but also on associated problems such as guilt, anger, grief and depression (e.g. psychodynamic therapies, PDT and non-directive counselling). In addition (c), trauma-focused (i.e. cognitive and behavioural) interventions are often integrated into a psychodynamic treatment.

RCTs on PTSD treatment in old age are very scarce. We identified two RCTs that examined this age group. An internet-based writing therapy called Integrative Testimonial Therapy (ITT) with WWII survivors combining cognitive-behavioural and life review elements found moderate decreases in PTSD symptoms [8, 9]. A prolonged exposure therapy with older veterans with PTSD as a result of their military service found treatment gains from pre- to posttest, but those gains were lost in the follow-up [10, 11].

Narrative approaches integrate exposure and cognitive interventions [e.g., [12]], their efficacy has been proven [13], but not in old age so far. Narrative approaches aim at reconstructing the memories of traumatic events and transforming them into a coherent narrative (exposure focus), integrating those memories into the biography and reassessing the meaning of the events (cognition focus).

#### Treatment of holocaust survivors in Israel

The most often offered treatment of Holocaust survivors in Israel is based on a psychodynamic understanding which integrates trauma-focused elements, i.e. imaginary or behavioural exposure, cognitive reappraisal and narrative techniques [14]. “Brief psychodynamic therapy” [15] is very often applied in the treatment of trauma patients. One randomised controlled trial (RCT) *without* older patients showed that it is more effective than the waiting list control group and similarly effective as trauma-focused therapy [16]. However, the treatments that have been shown to be effective in early and middle adulthood have just started to get systematically investigated in old age, and there is no randomised, controlled study with Holocaust survivors.

Amcha, the “National Israeli Center for Psychosocial Support of Survivors of the Holocaust and the Second Generation”, is a pioneer in helping and treating Holocaust survivors, and adapted an integrative psychodynamic approach [17]. Amcha has been founded in 1987 by a group of Holocaust survivors and mental health professionals with the goal (as a non-profit organisation) to support and treat survivors and their families with psychosocial interventions (mainly psychotherapy and social clubs). Amcha has steadily expanded over the 30 years of its existence. Today there are 15 centres in Israel that operate throughout the country. Most of the professionals are trained psychotherapists – psychiatrists, psychologists and social workers. About 8700 Holocaust survivors are currently treated by Amcha. Given the lack of efficacy studies of psychodynamic PTSD treatment in old age, it is needless to state that the efficacy of the treatment offered at Amcha has not been investigated so far.

#### Life review therapy as an age-specific treatment of PTSD

One approach to the treatment of *older* PTSD patients is to apply the established psychological therapies described above with minor adaptations [e.g., [11, 18]]. However, the question arises whether an age-specific treatment of PTSD would be more adequate. Aging is accompanied with reviewing one’s life in order to evaluate gains and losses and to find meaning [5]. Therefore, a narrative approach as mentioned above seems to meet very well the natural need of older people to review their lives [19]. Most studies on the efficacy of life review therapy (LRT) focus on late-life depression. A meta-analysis comparing the effect of life-review, CBT, PDT and other treatments on clinically depressed older adults found large effect sizes for LRT and CBT and medium effect sizes for PDT [20]. However, there is a lack of efficacy studies evaluating the effect of life-review therapy on PTSD symptoms in older individuals that have experienced traumatic events during their lives [19]. This is particularly surprising since there are very good experiences with narrative approaches in the treatment of PTSD with children, adolescents and young and middle-aged adults [13]. Maercker [21] combined the life-review therapy approach [22] with narrative exposure to the traumatic events such as in narrative exposure therapy [12]. He reported on three case studies that found this life-review therapy to be effective in German survivors of the Nazi period [21]. Building on these case studies, Knaevelsrud et al. [8] developed the Integrative Testimonial Therapy (ITT) approach, an internet-based writing therapy that integrates life-review therapy with narrative exposure and cognitive restructuring. Preliminary results of a pre-post follow-up study with a sample of older PTSD patients who were traumatised as children during WWII indicate that this therapy significantly reduces PTSD and anxiety symptoms.

While there is no controlled study on the efficacy of LRT with Holocaust survivors, experimental and narrative research on life stories of Holocaust survivors supports the assumption that it would be effective in this sample. For example, it was shown that the degree of disclosure during the telling of their story was positively correlated with long-term health [23]. Furthermore, in a longitudinal case study, one Holocaust survivor was systematically interviewed twice, in 1982 and 1995 [24]. It was found that while structure and general content of the narratives remain highly consistent over time, the later narrative was more fully developed and integrated new interpretations as well as historical insights. This qualitative finding suggests that Holocaust survivors might be open for re-evaluating their lives when reviewing major events.

### The need for a trial

From the previous literature review follows that not only the traditional, age-unspecific approaches (PDT, CBT), but also the age-specific LRT have not been evaluated with state-of-the-art methodology in Holocaust survivors. Therefore, an RCT that investigates the efficacy of LRT (as an age-specific trauma treatment) is urgently needed [25].

### Study objectives

To our knowledge, there is no controlled study evaluating the efficacy of psychotherapy in Holocaust survivors. Therefore, the general goal of this study is to evaluate the efficacy of an integrative, age-specific treatment of PTSD and related mental health problems (depression, anxiety, prolonged grief) in Holocaust survivors.

From the previous research outlined above follows that LRT, which not only meets the natural needs of older people to review their lives, but is also effective in the treatment of depression (as shown by several RCTs) and PTSD (as shown by case studies and preliminary results from one RCT), seems to be most promising for the treatment of Holocaust survivors.

Part of the basic support structure of Holocaust survivors in Israel are social support services, which are also provided by all Amcha centres throughout the country (called “social club”). The social clubs are meant to let survivors come together in an environment where they meet people with whom they share common experiences now and then. The clubs provide activities like films, lectures, courses in art, music, memory improvement, gymnastics, languages (English, Yiddish), visits to interesting places, birthday celebrations, discussions of relevant issues, etc. They are not intended for psychodynamic or trauma-focused psychotherapy.

Thus, in this study, participants receiving the treatment (LRT) are explicitly allowed to continue visiting the social club. The control group consists of social club member who receive no psychotherapeutic treatment (LRT or other). Control group participants might receive LRT after the follow-up assessment.

The goals of this study are:
to evaluate the effect of LRT for Holocaust survivors (LRT-HS), in addition to attending the “social club”, on symptoms of PTSD and related mental health problems (depression, anxiety, prolonged grief), compared to a supportive control group (“social club”);to identify groups of participants that seem to especially benefit from the treatment.

Two research questions will be investigated:
Does the LRT-HS as short-term treatment for Holocaust survivors, in addition to attending the “social club”, reduce the symptoms of PTSD and related mental health problems (depression, anxiety, prolonged grief) more than a supportive control group (only attending the “social club”)?

We expect that life-review therapy will reduce the symptoms of PTSD and related mental health problems with a large pre-post effect size and to a greater extent than the supportive control group at posttest and 6-months follow-up with a medium-to-large effect size.
2.Which factors moderate the treatment effect, i.e. which factors influence who benefits most from the intervention?

We expect that LRT-HS will have a greater effect in people (a) with more severe symptoms of PTSD, depression, anxiety and/or grief at pretest, (b) with lower positive well-being and posttraumatic growth at pretest, (c) of female gender, (d) with higher cognitive status at pretest, (e) with higher trauma severity, i.e. number of traumatic events, months/years experienced during the Holocaust, as well as traumatic experiences before and after the Holocaust.

## Methods/design

### Design

The proposed study is a randomised, controlled follow-up trial including Holocaust survivors with one or more stress-response disorders (i.e. PTSD, depression, anxiety and/or prolonged grief).

Participants will be randomly assigned (see Fig. 1) to either the LRT (in addition to the social club) or a supportive control group (social club only). The treatment includes 20–25 sessions. The participant timeline is presented as SPIRIT schedule in Fig. 1.

**Fig. 1 Fig1:**
[figure not shown]
SPIRIT schedule of enrolment, treatment, and assessments. Abbreviations: DASS-21: Depression Anxiety Stress Scale-21; GDS: Geriatric Depression Scale; LSI: Life Satisfaction Index; MMSE: Mini Mental Status Examination; PCL-5: PTSD Checklist for DSM-5; PHQ-9: Patient Health Questionnaire 9; PTGI: Posttraumatic Growth Inventory; PTCI: Posttraumatic Cognitions Inventory; PTSD: Posttraumatic stress disorder; RFS: Reminiscence Functions Scale

Enrolment into one of the two groups will be done consecutively during the recruitment phase. The treatment phase takes approx. Nine months. Before and after the treatment phase, participants in both groups will be assessed. Follow-up will take place at 6 month post-treatment. All assessments will be conducted by blind assessors.

### Sample

The sample consists of Holocaust survivors, i.e. Israeli individuals who were born in 1945 or earlier in Europe and experienced persecution, concentration camp, witnessed torture and death, or who survived in hiding and/or who experienced other traumatic events by the Nazi regime during WWII.

Each participant is diagnosed with either full or subsyndromal PTSD, depressive disorder (major depression, minor depression), anxiety disorder, or prolonged grief disorder.

#### Recruitment

The participants will be recruited from ten centres of Amcha in Israel. Mean age of Holocaust survivors attending the social club at Amcha centres is currently (in the year 2020) 89 years, the youngest were born in 1945. About 30% were born between 1935 and 1945 (now 75–85 years old), 50% between 1925 and 1935 (now 85–95 years old) and 20% were born before 1925 (now over 95 years old).

Study participants will be recruited from current and new social club members. During the time of the research project, there will be active advertisements in the community and at medical practices in order to introduce Amcha, its social clubs and the study treatment. The fact that Amcha is present in 15 cities across Israel, has a very good reputation in the country, and is working with other medical institutions, makes the proposed study highly feasible.

#### Inclusion and exclusion criteria

Inclusion criteria are:
Being a Holocaust survivor, i.e. born in 1945 or earlier in Europe and having experienced persecution, concentration camp, witnessed torture or death, or been forced to survive in hiding and/or experienced other traumatic events by the Nazi regime during WWII.Diagnosis of full or subsyndromal PTSD, depressive disorder (major depression, minor depression), anxiety disorder, or prolonged grief disorder.Participants do not receive any individual psychotherapy during the time of the study (except for LRT in the intervention condition).Participants must have been informed about the study and must have given written informed consent. This includes that he/she is willing to be randomly assigned to one of the study groups.

Exclusion criteria are: Probable dementia (Mini Mental Status Examination, MMSE < 26); acute psychotic disorder; acute suicidality.

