#### Sample size

Previous studies on PTSD treatments found a large mean effect size for PTSD outcomes (controlled *d* = 0.8 with a supportive control group) [26]. Studies on LRT also found a large mean (pre-post) effect size in older individuals with a mental disorder (in most studies depression) (g = 1.3; 19). We rest our sample size calculation on the conservative assumption of a medium-to-large effect size (d = 0.7, corresponds to f = 0.35). The sample size was calculated using G*Power 3.1.0 [27]. Given an α = 0.05 and a test power 1-β = 0.80, a total sample size of *n* = 50 (each group *n* = 25) is required. We assume a rather conservative drop-out rate of about 40% from enrolment to follow-up. Thus, we propose to start with 80 participants at enrolment (i.e. 40 in the LRT and 40 in the control group).

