#### Study outcome measures (primary and secondary endpoints)

All scales are applied in Hebrew language and have been tested for validity and reliability in this language. Primary endpoints are PTSD and depressive symptoms:
PTSD symptoms: The PTSD Checklist for DSM-5 (PCL-5) is used [29] in its Hebrew version [31], a 20-item self-report measure that assesses the 20 DSM-5 symptoms of PTSD.Depressive symptoms: The Patient Health Questionnaire (PHQ-9) and the Geriatric Depression Scale (GDS) are used. The PHQ-9 is a widely used 10-item self-report measure of depressive symptoms with well-established psychometric properties [32] in its Hebrew version [35]. The GDS is a 15-item self-report measure developed for use with older people [40]. It has been found reliable and valid in an Israeli sample [41].

Secondary endpoints are:

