### Data analysis

#### Statistical analysis

Several analytic strategies are planned to test the efficacy of the treatment. First, analyses of variance (ANOVAs) will be conducted to compare the mean outcome in PTSD and depressive symptoms (primary endpoints) as well as the secondary endpoints. The age at the time of trauma, gender, educational level, cognitive status and trauma severity will be considered as covariates.

Secondly, individual growth curves will be analysed, i.e. rates and shapes of change will be examined, and individual growth curves will be compared to investigate differences.

Thirdly, multivariate analyses will be used to test the effect of the treatment with regard to primary and secondary outcomes. In this way, correlations between the outcome measures can be considered. Post hoc analyses will be performed following a significant overall effect.

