#### Methods against bias

The proposed study requires several methods to avoid bias.

Selection bias: The randomisation procedure is the gold standard to avoid this bias. Random numbers will therefore be generated in advance. The randomisation procedure will be controlled by comparing the two groups with regard to possible confounders, i.e. age at the time of trauma, gender, educational level, diagnosis, cognitive status and trauma severity.

Detection bias: The baseline assessment is done before randomisation to avoid this bias. In addition, the therapists will not collect any outcome data at posttest and follow-up. This will be done by blinded members of the research team (clinical psychologists or psychiatrists or advanced master students in clinical psychology).

Performance bias: To counteract this bias, the standardisation procedure (manual, extensive training, documentation of sessions, supervision) is established.

Attrition bias: Statistical analysis will include techniques to minimise possible attrition bias, i.e. intention-to-treat analysis and imputing missing data. In case of drop-outs, it is intended to continue data collection whenever possible.

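### Entry on any of four diagnoses, with PTSD and depression as primary endpoints for everyone: d = 0.7 makes no stated allowance for the mixed sample, and entry diagnosis is not among the covariates

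*Protocol article*

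**What the plan says.** All references are to the protocol article.

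- **Entry.** Inclusion and exclusion criteria: "Diagnosis of full or subsyndromal PTSD, depressive disorder (major depression, minor depression), anxiety disorder, or prolonged grief disorder". One is enough, and the Design and Sample sections agree. PTSD may be subsyndromal and depression may be minor.
- **Endpoints.** Study outcome measures: "Primary endpoints are PTSD and depressive symptoms". These are scored on the PCL-5 and on the PHQ-9 and GDS. Grief and anxiety are secondary. No endpoint is restricted by entry diagnosis.
- **Planning effect.** Sample size: "Previous studies on PTSD treatments found a large mean effect size for PTSD outcomes", given as a controlled d = 0.8. The second source is a pre-post g = 1.3 from life-review studies in older people with a mental disorder, mostly depression. The plan then uses d = 0.7, called conservative, for 50 evaluable participants and 80 enrolled.
- **Covariates.** Statistical analysis: "The age at the time of trauma, gender, educational level, cognitive status and trauma severity will be considered as covariates".
- **Balance check.** Methods against bias compares the groups on "possible confounders, i.e. age at the time of trauma, gender, educational level, diagnosis, cognitive status and trauma severity". This is the covariate list plus diagnosis.
- **Moderation.** Study objectives, hypothesis (a), expects a larger effect in people with more severe symptoms at pretest.

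**The concern.** Two of the four entry routes, anxiety alone and prolonged grief alone, match neither primary endpoint. The other two match only one each: someone with depression only is a mismatch on the PCL-5, and someone with PTSD only is a mismatch on the depression scales. The effect size comes from studies where outcome and disorder largely coincide. The protocol's own hypothesis (a) implies a smaller effect in people with few symptoms on the scale in question, but the Sample size section does not carry that through.

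Two things are at stake. Power on each primary endpoint may be below the planned 0.80. And a difference over all participants on the PCL-5 does not by itself show whether life-review therapy reduces PTSD in those who have it, which the Background presents as the gap in the evidence. Entry diagnosis is known before randomisation and probably predicts the outcome scores, yet it is not among the covariates.

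**Working it through.** **Inputs.** From the Sample size section: d = 0.7 (f = 0.35), cited d = 0.8, alpha 0.05, power 0.80, N = 50 evaluable, 80 enrolled. Assumed, because the article does not give them: q, the share without the disorder that an endpoint measures; and r, the effect in that share relative to the rest. The SD is taken as equal in both.

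**1. Reproducing N = 50.** Neither test nor sidedness is stated. A between-group repeated-measures ANOVA has noncentrality λ = f²·N·m / (1 + (m − 1)ρ). With m = 2 measurements and ρ = 0.5, λ = 0.1225 × 50 × 2 / 1.5 = 8.17, which gives power 0.7996. With m = 3 and ρ = 0.6, N = 50 reaches 0.80. A one-sided t-test needs 52. A two-sided t-test needs 68 and has power 0.68 at 50. The stated figure is reproduced by the repeated-measures form, which is used in step 2.

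**2. Effect over all participants.** d(all) = 0.7 × [(1 − q) + r·q]. For q = 20% and r = 0: 0.7 × 0.8 = 0.56.

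| q | r = 0: d, power at 50, N for 0.80 | r = 0.5: d, power at 50, N for 0.80 |
|---|---|---|
| 0% | 0.70, 0.80, 52 | 0.70, 0.80, 52 |
| 10% | 0.63, 0.71, 62 | 0.665, 0.76, 56 |
| 20% | 0.56, 0.61, 78 | 0.63, 0.71, 62 |
| 30% | 0.49, 0.50, 102 | 0.595, 0.66, 70 |
| 50% | 0.35, 0.29, 196 | 0.525, 0.56, 88 |

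(N in even steps; the first row is 0.7996 at 50, hence 52.)

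**3. What the reduction from 0.8 to 0.7 absorbs.** If 0.8 holds in those with the disorder, solve 0.8 × [1 − q(1 − r)] = 0.7, so q(1 − r) = 0.125. That is q = 12.5% at r = 0, or q = 25% at r = 0.5.

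**4. Would restricting each endpoint to matching cases be better?** Two-sided t-test, d = 0.7 in cases, p = 1 − q the share of cases:

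| p | All 80: r = 0 / 0.5 / 0.75 | Cases only, of 80 | Cases only, of 50 |
|---|---|---|---|
| 80% | 70 / 79 / 84% | 79% | 58% |
| 60% | 46 / 70 / 79% | 66% | 46% |
| 50% | 34 / 64 / 77% | 58% | 39% |

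The subset has more power when non-cases gain nothing. At half the effect the two are level (p = 80%) or all participants do better (70 v 66%, 64 v 58%). Beyond that the subset loses clearly.

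**5. Gain from the covariate.** Two yes/no terms cost two degrees of freedom. If they explain a share R² of the remaining variance, the standard error is multiplied by √(1 − R²). An illustrative simulation of a posttest comparison gave a reduction of roughly 3–10%, which corresponds to R² of 1 − 0.97² = 0.06 to 1 − 0.90² = 0.19. If change from pretest is analysed, there is little left to gain.

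**The case against.** The strongest defence is that the broad sample is deliberate. The stated aim is PTSD and related problems in Holocaust survivors with at least one stress-response disorder, and the comparison of everyone randomised answers that question. This stands, and it is why the primary population should not change.

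Second, the planned effect was already set below the cited 0.8. That stands in part: step 3 shows how much dilution it covers. But the Sample size section does not tie the reduction to the case mix.

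Third, Statistical analysis and Methods against bias do not contradict each other: one lists model covariates, the other a check of balance. That is right. The case for adding diagnosis is that it is free information, not that the text conflicts. Final covariates may also be settled in an analysis plan that is not shown.

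Stronger readings are tempting but unsupported:

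- *The effect is certainly diluted.* No case mix is given. Every participant must have lived through Nazi-era persecution or other trauma, and the Background describes survivors who seek treatment as showing depressed or irritable mood from underlying PTSD. Comorbid symptoms are therefore plausible in people who enter on anxiety or grief.
- *Those without the diagnosis start near the floor and cannot improve.* Being below a diagnostic threshold does not mean a minimal score on a severity scale, and the article gives neither a cut-off for subsyndromal PTSD nor baseline scores. Less room to improve is as far as one can go. For the same reason it is speculation that floor effects alone would confirm hypothesis (a).
- *Each primary claim should move to the diagnosed subset.* Step 4 shows a trade-off that can lose power.

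**Conclusion.** The mismatch between entry criteria, primary endpoints and the source of the effect size is real, and the article makes no stated allowance for it. The likely direction is a smaller effect over all participants, consistent with the protocol's own hypothesis (a). The size is unknown. With d = 0.7 in those with the disorder, equal SDs and the repeated-measures form that reproduces N = 50, power falls from 0.80 to 0.61 or 0.50 when 20% or 30% lack the disorder and gain nothing, and to 0.71 or 0.66 when they gain half. If the true effect in cases is 0.8, there is no loss against plan until 12.5% gain nothing or 25% gain half. None of this shows that the trial is underpowered. It shows that d = 0.7 has not been justified for the sample that will be enrolled, and that an inexpensive adjustment for entry diagnosis has been left out.

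**What to change.** 1. **Statistical analysis:** add entry diagnosis to the covariates as two terms, full or subsyndromal PTSD (yes/no) and major or minor depression (yes/no), both established before randomisation.
2. **Population:** keep all randomised participants as primary for both endpoints. Add as supportive analyses the PCL-5 comparison in those with full or subsyndromal PTSD at pretest, and the comparison on the depression scales in those with major or minor depression at pretest.
3. **Sample size:** give the expected case mix, and either say that d = 0.7 assumes participants with the target disorder or justify it for the mixed sample.

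No new data or participants are needed. The costs are about two degrees of freedom, low precision in the supportive subsets (38% to 58% power at 50 completers if half to four fifths are cases; step 4 rounds the lower figure to 39%), and a less favourable stated effect for all participants.
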